### Potential harms and patient safety

We do not expect any specific complications or harms for patients because only non-evidence-based medications will be discontinued. However, there is a slight possibility that the discontinuation of a drug might lead to reappearance or development of new symptoms. In this case, the medication can be restarted at any time at the discretion of the GP. The PRIMA-eDS tool only provides recommendations based on current best evidence. The decision about the medication always remains with the GP in agreement with the patient. Nevertheless, we monitor potential harms. GPs are required to report serious adverse events in the eCRF as soon as they get notice of the event, and all adverse events at the scheduled study visits. They are asked to judge whether the adverse event is associated with the intervention. All serious adverse events will be reported to the SDMC for final analysis and judgment.

### Data management and sample size calculation

Sample size calculation is based on binary analysis of the primary endpoint (non-elective hospital admission or death within 2 years). The study sets out to prove superiority regarding the primary endpoint. Garfinkel observed an 18 % absolute risk reduction achieved by prudent reduction of polypharmacy in a non-randomized controlled trial (from 30 % in the control group to 12 % in the intervention group regarding the annual referral rate to acute care facilities) [23]. This corresponds to a relative risk reduction of 60 % regarding this endpoint.

However, considerably smaller reductions than this still represent substantial clinical and economic benefits; therefore, this study is powered to detect a relative risk reduction of 20 %. We expect to recruit healthier patients than Garfinkel and will use non-elective hospital admission (yes/no) instead of referral rate, because it seems less susceptible to bias. In addition, our primary outcome will combine mortality with hospital admission, since there may be trade-off between these. We have been unable to find empirical data on which to estimate the rate of admission and mortality for our population, but in England in 2010 there was an average of approximately one completed consultant episode for every person in the population aged 75 years or older [43]. The primary outcome of dropouts is coded as an ‘event’ in both groups. Therefore, we consider a low estimate to be half the rate observed by Garfinkel [23]: an annual admission and mortality rate of 15 % of control patients; or 30 % in 2 years. Calculations show that in the event of the actual rate being higher than this, the sample size given below is conservative (ie., larger, rather than smaller, than requirement).

A relative risk reduction of 20 % in the intervention group implies a 2-year event rate of 24 % for that group.

The sample size is calculated according to Hayes et al. [44] for a power of 80 % (1-*β* = 0.8), *α* =5 %, and an assumed intra-cluster correlation coefficient (for similarity in outcomes between patients within GP practices) of no more than 0.01 (derived from an earlier cluster-randomized trial involving GP practices as clusters [45]). Dropouts in both groups will be considered as treatment failures. Further assuming attrition rates of 10 % of patients and 10 % of GP practices over the period of the study, sample sizes required at recruitment are 3542 patients (1771 per arm) across 322 GP practices at a mean of 11 patients per GP practice (Poisson random variation in patient numbers per GP practice is assumed). To operate a practicable number of GP practices and patients per country we are aiming at 325 GP practices (65 per study center) recruiting 3575 patients (11 patients per GP practice). See Additional file 1: Figure S1.

We will record all data in the PRIMA-eDS eCRF and store them in a XML-database in a secure central server provided by Avain technologies (http://www.avaintec.com/?lang=en). To monitor data quality, we will transfer data to the Department of Medical Informatics, Biometry and Epidemiology, Ruhr University, Bochum, Germany, every week throughout the trial. Statistical analyses will only be carried out after the end of the trial, with no interim analysis planned. Upon completion of data collection, Avain technologies will provide a final file for statistical analysis.

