### Primary outcome

The primary outcome is a composite endpoint of first non-elective hospital admission or death during the observation period measured as a binary outcome. This avoids issues of a potential trade-off between these two forms of event and also allows all patients to be included in the primary analysis. Primary outcome measures are recorded by the GPs when they occur or at follow-up visits every 8 months.

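### The 2-year control rate of 30% is twice 15% a year, but for a first-event outcome a constant 15% annual risk gives 27.75%, where power at the planned size is about 74%

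*Protocol article*

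**What the plan says.** The Primary outcome section defines a "composite endpoint of first non-elective hospital admission or death during the observation period measured as a binary outcome". The section on data management and sample size bases the calculation on a binary analysis of that endpoint over 2 years.

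For the control arm it takes half the annual referral rate seen in a non-randomised study of medication reduction, calls this a low estimate, and writes it as "an annual admission and mortality rate of 15 % of control patients; or 30 % in 2 years". It then says: "A relative risk reduction of 20 % in the intervention group implies a 2-year event rate of 24 % for that group". The other inputs are:

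- 80% power and 5% alpha (two-sided, from the Statistical analysis section);
- an intra-cluster correlation of at most 0.01;
- a mean of 11 patients per practice, with Poisson variation;
- attrition of 10% of patients and 10% of practices, with dropouts counted as treatment failures.

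The result is 1771 patients per arm in 322 practices, with a working target of 325 practices. The section adds that the size is conservative if the true rate proves higher than assumed.

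**The concern.** Doubling an annual figure suits a count of events, where one patient can contribute in both years. It does not suit a first-event outcome, because patients who have already had the event are no longer at risk of a first one. A 15% risk in each year must be compounded, and the result is below 30%.

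The control rate drives the sample size, and the 20% relative reduction is applied to it. A lower control rate means a smaller absolute difference and so less power from the same number of practices. The sentence on conservatism looks only upwards from 30%, whereas the compounded figure lies below it. A reader of a null result would then judge it against 80% power, which does not follow from 15% a year at constant risk.

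**Working it through.** **Step 1. Inputs.** From the sample size section: control 15% a year, written as 30% in 2 years; intervention 24%; ICC 0.01; m = 11; 161 practices and 1771 patients per arm; attrition 10% of patients and 10% of practices; dropouts as failures. Combined attrition is 1 − 0.9 × 0.9 = 19%. Combining the two rates in this way is my inference, and Step 2 tests it.

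**Step 2. Reproduce the stated size.** With 19% counted as events in both arms:

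- p0 = 0.19 + 0.81 × 0.30 = 0.4330
- p1 = 0.19 + 0.81 × 0.24 = 0.3844
- difference = 0.0486
- sum of p(1 − p) = 0.2455 + 0.2366 = 0.4821

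The Hayes cluster formula is n per arm = (1.960 + 0.842)² × [p0(1 − p0) + p1(1 − p1)] × DE / (p0 − p1)², where DE = 1 + (11 − 1) × 0.01 = 1.10, or 1 + 11 × 0.01 = 1.11 for Poisson cluster sizes.

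- DE 1.10: 7.849 × 0.4821 × 1.10 / 0.002362 ≈ 1762 per arm (160.2 practices)
- DE 1.11: ≈ 1778 per arm (161.7 practices)

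The stated 1771 lies between these. Adding the formula's one extra cluster per arm gives 161.2 to 162.7 practices. Power at 1771 per arm is 79.6% to 80.2% over these variants, so the plan's 80% is correct for 30% versus 24%. Inflating by 1/0.81 without counting dropouts as events gives only about 1162 to 1303 per arm and does not reproduce the plan.

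**Step 3. Two-year risk from 15% a year.**

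- Constant annual risk: 1 − 0.85² = 0.2775; × 0.8 = 0.2220
- Rate per person-year: 1 − exp(−0.30) = 0.2592; × 0.8 = 0.2073
- Year-2 risk among event-free patients needed to reach 30%: 0.15 / 0.85 = 17.6%

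The protocol applies the 20% reduction to the 2-year risk, and so do I.

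**Step 4. Power at the planned size.** For 27.75% versus 22.2%:

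- p0 = 0.19 + 0.81 × 0.2775 = 0.4148
- p1 = 0.19 + 0.81 × 0.2220 = 0.3698
- difference = 0.81 × 0.0555 = 0.04496
- sum of p(1 − p) = 0.2427 + 0.2331 = 0.4758
- standard error (DE 1.10) = √(0.4758 × 1.10 / 1771) = 0.01719
- z = 0.04496 / 0.01719 = 2.615; power = Φ(2.615 − 1.960) = 74.4%

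| 2-year risks before dropout coding | Power at 161 practices per arm |
|---|---|
| 30% vs 24% | 79.6% to 80.2% |
| 27.75% vs 22.2% | 73.7% to 74.4% |
| 25.92% vs 20.73% | 68.4% to 69.1% |
| 35% vs 28% | 89.6% to 90.0% |

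The ranges cover both design effects, with and without the extra cluster. At the 325-practice target, power for 27.75% versus 22.2% is 74.1% to 74.8%. For scale, 80% power at those rates would take about 185 to 188 practices per arm, against 161.

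**The case against.** The protocol sizes the trial on 2-year rates of 30% and 24%, and at those rates its power is right. The 27.75% needs an assumption that the text does not make: the same 15% risk in year 2 among patients still event-free. If 15% of the original control patients had a first event in each year, the sum would be exactly 30%. The implied year-2 risk of 17.6% is not far-fetched in patients aged 75 or older, since those expected to live less than a year are excluded at entry. The rate is also an admitted judgement, made without empirical data and labelled low, and 2.25 percentage points are small beside that uncertainty. At 35% versus 28% power would be about 90%.

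Much of this stands. It means that 74% is a conditional figure and that 30% may be a reasonable planning value. It does not supply the missing step: the article gives no reason for a higher second-year risk and offers the 30% only as a restatement of 15% a year. Calling the annual rate low does not justify the conversion, and the remark on conservatism does not reach below 30%.

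A reader might infer that the power calculation itself is wrong, or that the trial is shown to be underpowered. The documents support neither: the calculation reproduces, and the true rate is unknown.

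**Conclusion.** The conversion from 15% a year to 30% in 2 years is wrong as written for a binary first-event outcome, unless the second-year risk is higher, which the protocol does not say. At a constant annual risk the design rates are 27.75% and 22.2%, and power at 1771 per arm is about 74% instead of 80%. Reading 15% as a rate per person-year lowers it to about 69%.

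These figures rest on three assumptions: constant risk over the 2 years, ICC 0.01 with 11 patients per practice, and 19% attrition counted as events in both arms. The last is inferred from the stated dropout rule and supported by the match to the planned size.

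It may be tempting to conclude that the dropout rule should be changed to win back power. That would alter the primary analysis and is a separate matter; it does not follow from this point.

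**What to change.** Change the sample size paragraph in one of two ways.

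1. Replace 30% and 24% by 27.75% and 22.2%, and restate the power as about 74% at the planned size with the present dropout rule.
2. If 30% is the intended 2-year risk, state it directly with its reason, remove the derivation from 15% a year, and report that power falls to about 74% at 27.75%.

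In either case, say that the remark on conservatism does not extend to rates below the assumed one. The cost is a few sentences and, under the first option, a less favourable stated power. Neither option changes recruitment, the endpoint or the analysis.

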### Statistical analysis

Statistical analyses are elaborated in a prespecified statistical analysis plan. The binary primary outcome will be analyzed following intention-to-treat principles; secondary outcomes per protocol. A suitable generalized mixed model will be used to account for cluster randomization. Additionally, the study center as fixed factor is included to avoid confounding through stratified randomization. A two-sided *α* of 5 % will be used throughout.

The intervention could result in mortality rates differing between the two trial arms, which could bias analyses of other outcomes if simple exclusion were to be applied. If we find evidence for differential mortality, analysis of secondary outcomes will employ appropriate adjustment methods [46].

Besides a per protocol analysis of the primary outcome, further sensitivity analyses will be undertaken to assess the stability of the results to the model specification, including time-to-event and counts of events analyses as well as patient and GP practice covariates found to be unbalanced across the two trial arms. Random imputation methods will be used, to investigate the sensitivity of the chosen method for replacement of missing values for dropouts in the primary endpoint.

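### The 80% power counts patients of departed practices as events but keeps the ICC at 0.01; on that reading, power at the stated rates and attrition is about 43%

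*Protocol article*

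**What the plan says.** All inputs stand in the protocol article, under *Data management and sample size calculation* unless noted.

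- Control rate: "an annual admission and mortality rate of 15 % of control patients; or 30 % in 2 years".
- Effect: "A relative risk reduction of 20 % in the intervention group implies a 2-year event rate of 24 % for that group".
- Method: "The sample size is calculated according to Hayes et al. [44] for a power of 80" per cent, with α of 5%. *Statistical analysis* adds: "A two-sided *α* of 5 % will be used throughout".
- Clustering: "an assumed intra-cluster correlation coefficient (for similarity in outcomes between patients within GP practices) of no more than 0.01", taken from an earlier cluster trial in GP practices.
- Dropouts: "Dropouts in both groups will be considered as treatment failures". The preceding paragraphs give the same rule for the primary outcome. Neither statement makes an exception.
- Attrition and result: "Further assuming attrition rates of 10 % of patients and 10 % of GP practices over the period of the study, sample sizes required at recruitment are". The figures given there are 1771 per arm, 3542 in all, over 322 practices with a mean of 11 patients and Poisson variation in practice size. The operational target is 325 practices and 3575 patients.

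The primary analysis is an intention-to-treat comparison of a binary outcome by a generalized mixed model. Random imputation for dropouts is planned as a sensitivity analysis.

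**The concern.** The event coding acts on the calculation in two ways. It raises both event rates and narrows the difference between them, and the printed sample size already pays for that. It also acts on the clustering. When a whole practice leaves and its patients all receive the value 1, their outcomes are identical by construction. An ICC borrowed from another trial's outcome does not contain that, and no allowance for it is stated.

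If one practice in ten behaves this way, the variance between practices is many times what an ICC of 0.01 implies. The trial could then be more likely than not to miss the effect it was sized for, while the article reports 80% power.

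**Working it through.** **1. Reproduce the printed number.** Combined attrition is 1 − 0.9 × 0.9 = 19%. With all of it coded as events:

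- control: 0.81 × 0.30 + 0.19 = 0.433, variance 0.433 × 0.567 = 0.2455
- intervention: 0.81 × 0.24 + 0.19 = 0.3844, variance 0.3844 × 0.6156 = 0.2366
- difference: 0.0486

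The design effect is 1 + (11 − 1) × 0.01 = 1.10. Practices per arm by the cited cluster method:

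c = 1 + (1.960 + 0.842)² × (0.2455 + 0.2366) × 1.10 / 11 / 0.0486² = 161.2

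The article has 161, and 161 × 11 = 1771. Power at 1771 per arm with design effect 1.10 is 80%.

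**2. Try the other natural readings** (ICC 0.01 throughout).

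- All dropouts left out, 30% against 24%, inflated for loss: about 106 to 107 practices per arm.
- Patient dropouts coded as events (0.37 against 0.316), lost practices removed: 121.9 / 0.9 = about 135 per arm.

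Neither is near 161.

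**3. ICC of the coded outcome.** Let q = 0.9p + 0.1 be the event rate in practices that stay: 0.37 (control) and 0.316 (intervention). A practice leaves with probability 0.1 and then has rate 1.

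Between-practice variance = 0.1 × 0.9 × (1 − q)² + 0.9 × 0.01 × q(1 − q)

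- control: 0.0357 + 0.0021 = 0.0378; divided by 0.2455, ICC = 0.154; design effect 1 + 10 × 0.154 = 2.54
- intervention: 0.0421 + 0.0019 = 0.0441; divided by 0.2366, ICC = 0.186; design effect 2.86

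Practice departure alone, without the assumed 0.01, gives 0.146 and 0.178.

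**4. Power at 1771 per arm.**

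SE = √[(0.2455 × 2.54 + 0.2366 × 2.86) / 1771] = 0.0271

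0.0486 / 0.0271 = 1.793; 1.793 − 1.960 = −0.167; power = Φ(−0.167) = 43%

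Allowing for Poisson practice sizes it is 41%. Simulation with Poisson sizes gives 42.6% for a t-test on practice means and 42.6% for a random-intercept logistic model, the type of analysis planned. The target of 3575 patients gives about 42% to 44%. If the same 19% dropped out independently of practice, power would be about 80%, so whole-practice departure causes the loss.

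**5. Sensitivity** (patient attrition 10%, relative reduction 20%, 1771 per arm, equal practice sizes).

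| Practice loss | Control rate | Power |
|---|---|---|
| 10% | 30% | 43% |
| 5% | 30% | 61% |
| 2% | 30% | 78% |
| 10% | 40% | 72% |
| 10% | 50% | 93% |

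**6. Power under other handling** (ICC 0.01, 10% and 10% attrition, loss unrelated to outcome).

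- Lost-practice patients left out, individual dropouts still events: 0.37 against 0.316 with 0.9 × 1771 = 1594 per arm; SE 0.0176; power about 87%.
- All dropouts left out: 30% against 24% with 0.81 × 1771 = 1435 per arm; SE 0.0173; power about 93%.

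**The case against.** The strongest objection is that the article never says outright that every patient of a departed practice is a dropout. It names dropouts in one sentence and practice attrition in the next, and *Monitoring* provides for reported dropouts to be checked by telephone, so some outcomes might still be obtained. This stands as a caveat: the coding of lost practices is a reading. It is well supported, because the rule has no exception and the printed number fits no other natural reading. The fit is close but not exact: 161.2 is rounded down, and the Poisson variation that the article assumes would give about 162.7.

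Second, the article calls 30% a low estimate and says that a higher rate makes the size conservative. The direction is right, since power rises to 72% at 40% and 93% at 50%. But the 80% is claimed at 30%. The 10% practice loss is likewise a planning allowance, and smaller loss would hurt less.

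Third, practice-level loss may be treated in the statistical analysis plan, which is not shown. That cannot repair a power figure whose rates, attrition, coding rule and sample size are all fixed in the article. The planned random imputation is a sensitivity analysis and leaves the power of the primary analysis unchanged.

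A reader might also infer an arithmetic slip. There is none: the printed number follows from its inputs, but the ICC does not match the outcome as coded.

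**Conclusion.** The stated 80% does not hold under the article's own attrition and coding rule. At 30% against 24%, with 10% of practices lost and all their patients coded as events, power at 1771 per arm is about 43%.

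The figure rests on three things: that patients of a departed practice fall under the dropout rule, that the full 10% of practices leave, and that the control rate is the planned 30%. A reader might infer that the trial has 43% power whatever happens. The documents do not support that, because practice loss and the control rate are planning values and power ranges from 43% to 93% over the values shown. What is established is that the power statement contradicts the assumptions printed beside it. The arithmetic is secure; the reading of practice loss is an inference, though a strong one.

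**What to change.** Choose one of two changes.

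1. **Keep the coding rule and restate the power.** Give about 43% under the stated rates, attrition and rule, with the sensitivity range above, and say explicitly whether patients of departed practices count as dropouts. This costs only wording, but it concedes low power at the planning values. Restoring 80% under the rule would take about 4,320 to 4,600 patients per arm (about 393 to 418 practices).

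2. **Change the primary analysis** so that patients of departed practices are not all coded as events. Multiple imputation of their outcomes is one option, with event coding kept as a sensitivity analysis. Then restate power for the method chosen. As a guide, power is about 87% if only lost-practice patients are no longer coded as events and are left out. The 93% applies only if event coding is dropped for all dropouts, which abandons the rule as a whole, and must not be quoted for the narrower change. Both figures assume ICC 0.01 and loss unrelated to outcome.

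The second change needs no added recruitment. Its price is a missing-at-random assumption in an unblinded trial. If patients are left out rather than imputed, it also departs from strict intention-to-treat and from the aim, stated under *Primary outcome*, of including every patient.

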### Statistical analysis

Statistical analyses are elaborated in a prespecified statistical analysis plan. The binary primary outcome will be analyzed following intention-to-treat principles; secondary outcomes per protocol. A suitable generalized mixed model will be used to account for cluster randomization. Additionally, the study center as fixed factor is included to avoid confounding through stratified randomization. A two-sided *α* of 5 % will be used throughout.

The intervention could result in mortality rates differing between the two trial arms, which could bias analyses of other outcomes if simple exclusion were to be applied. If we find evidence for differential mortality, analysis of secondary outcomes will employ appropriate adjustment methods [46].

Besides a per protocol analysis of the primary outcome, further sensitivity analyses will be undertaken to assess the stability of the results to the model specification, including time-to-event and counts of events analyses as well as patient and GP practice covariates found to be unbalanced across the two trial arms. Random imputation methods will be used, to investigate the sensitivity of the chosen method for replacement of missing values for dropouts in the primary endpoint.

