### Objectives of the study

Our principal hypothesis is that the reduction of polypharmacy and inappropriate prescribing will improve clinical outcomes for older patients. The primary objective is to test this hypothesis by the evaluation of the PRIMA-eDS tool in a multicenter cluster-randomized controlled trial with the combined primary endpoint of first non-elective hospital admission or death (see Table 1).

**Table 1 Tab1:** PICO research question of the PRIMA-eDS trial

PICO-Item	Research question
P (patients)	Patients aged ≥75 years taking ≥8 drugs in primary care
I (intervention)	GPs of enrolled patients with access to the PRIMA-eDS tool
C (comparison)	GPs of enrolled patients without access to the PRIMA-eDS tool (usual care)
O (outcome)	Non-elective hospitalization or death within an observation time of 2 years

*PRIMA-eDS* Polypharmacy in chronic diseases–Reduction of Inappropriate Medication and Adverse drug events in older populations by electronic Decision Support

Secondary objectives are to evaluate the effectiveness of the decision support tool regarding all-cause mortality and non-elective hospital admission as single endpoints as well as a number of secondary outcomes (see Methods section).

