### Blinding

Inherent to the study protocol GPs and patients cannot be blinded. The analyst will be kept blind to GP practice allocation.

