### Secondary outcome

Secondary endpoints are all cause mortality, non-elective hospital admission (number of episodes and duration), falls (number and severity), fractures, quality of life (SF-12v2), the number and types of drugs (total number, number discontinued, number not discontinued despite the recommendation to discontinue, number re-administered for symptom control), adverse event rate, and medication costs over the observation period.

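### Per protocol is the only analysis set stated for the secondary outcomes, including all-cause mortality, non-elective admission and the adverse event rate, so these comparisons lose the protection of randomisation

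*Protocol article*

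**What the plan says.** The Statistical analysis section assigns the analysis sets in one sentence: "The binary primary outcome will be analyzed following intention-to-treat principles; secondary outcomes per protocol". The Secondary outcome section shows what falls under the second half. Its list begins "Secondary endpoints are all cause mortality, non-elective hospital admission (number of episodes and duration), falls (number and severity), fractures" and ends "adverse event rate, and medication costs over the observation period". Objectives of the study gives two of these outcomes special weight, since a secondary aim is to "evaluate the effectiveness of the decision support tool regarding all-cause mortality and non-elective hospital admission as single endpoints".

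Per protocol here means an analysis set, not simply 'as the protocol describes'. The same section sets it against intention to treat and lists it as a sensitivity analysis for the primary outcome: "Besides a per protocol analysis of the primary outcome, further sensitivity analyses will be undertaken". The remaining sensitivity analyses in that paragraph concern the primary analysis and its missing values. The one safeguard for secondary outcomes is conditional: "If we find evidence for differential mortality, analysis of secondary outcomes will employ appropriate adjustment methods".

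**The concern.** A per-protocol set is selected by what happens after randomisation. Three features of this trial make that selection a practical worry.

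- **Unequal demands.** Under Follow-up, intervention GPs must repeat the tool-based review at each follow-up visit and at the final visit. Control GPs continue usual care and record data. Tool use is thus a requirement that exists in one arm only.
- **Open label.** The Blinding section says: "Inherent to the study protocol GPs and patients cannot be blinded".
- **Prognosis.** The patients are 75 or older on at least eight drugs. It is plausible that frail or dying patients miss reviews more often, although the protocol gives no figure.

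Three things are at stake. First, death and admission were combined because one might be traded for the other, so the components are needed to interpret the composite. They would come from a different, non-randomised set of patients. Second, the protocol accepts that stopping a drug may bring symptoms on or back. If such patients leave the protocol, their events may leave the comparative adverse event rate. Third, the abstract says the trial should show whether GPs and patients will follow the recommendations, and a set selected on adherence could remove those who did not.

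**Working it through.** **The plan's own figure.** The concern disputes no number, but the sample size fixes the arm size used below, so it was reproduced first. Inputs from the sample size section: 30% against 24% events, two-sided 5%, power 80%, intra-cluster correlation 0.01, mean cluster size 11, attrition of 10% of patients and 10% of practices, dropouts coded as events.

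- Combined attrition: 1 − 0.9 × 0.9 = 0.19.
- Diluted rates: 0.19 + 0.81 × 0.30 = 0.433 and 0.19 + 0.81 × 0.24 = 0.3844.
- Two-proportion formula: 1605 per arm.
- Design effect: 1 + (11 − 1) × 0.01 = 1.10, and 1605 × 1.10 = 1765.5.
- 1765.5 / 11 = 160.5, rounded up to 161 practices; 161 × 11 = 1771 per arm, or 3542 patients in 322 practices. This matches the plan.

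**Illustration for mortality.** From the plan: 1771 per arm and design effect 1.10. Assumed, because the document gives none of these: no true effect, 12% two-year mortality in both arms, and excluded patients at twice the mortality of those retained. If a fraction e of an arm is excluded and retained patients have mortality m, then m(1 − e) + 2m·e = 0.12, so m = 0.12 / (1 + e).

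SE = √{[m₁(1 − m₁)/n₁ + m₀(1 − m₀)/n₀] × 1.10}, z = (m₀ − m₁)/SE, and the chance of a false finding of benefit is P(Z > 1.96 − z).

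| Excluded, intervention / control | m₁ | m₀ | n₁ / n₀ | Risk ratio | SE | z | False benefit |
|---|---|---|---|---|---|---|---|
| 20% / 0% | 0.100 | 0.120 | 1417 / 1771 | 0.83 | 0.0116 | 1.72 | about 40% |
| 20% / 10% | 0.100 | 0.109 | 1417 / 1594 | 0.92 | 0.0117 | 0.78 | about 12% |
| 20% / 20% | 0.100 | 0.100 | 1417 / 1417 | 1.00 | 0.0118 | 0 | 2.5% |

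If the second row is reversed (10% / 20%), the risk ratio is 0.109/0.100 = 1.09 and the roughly 12% becomes a false finding of harm. If excluded patients have the same mortality as those retained, the expected risk ratio is 1.00.

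**Range.** With no control exclusions, 15% mortality, doubled mortality in the excluded and design effect 1.11 (Poisson cluster sizes), excluding 10%, 20% or 30% of the intervention arm gives risk ratios of 0.91, 0.83 and 0.77. The chance of false benefit is about 19%, 49% and three quarters. Over mortality of 10 to 20%, exclusions of 10 to 30% and relative mortality of 1.5 to 3, the risk ratio runs from 0.95 to 0.63 and false benefit from 6% to nearly 100%. Analysed as randomised, the expected risk ratio is 1.00 and the chance of false benefit 2.5% throughout.

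**The case against.** The strongest reply is that the document does not define the per-protocol set; that definition may stand in the analysis plan, which is not shown. A reader might infer that exclusions fall on the intervention arm alone. The text does not support that: control GPs record data at the same time points (Control section), and the monitoring of visit adherence makes no distinction by arm. Missed visits or eligibility violations could remove controls as well. Overriding the tool is left to GP and patient, so it is not clearly a deviation. Whole practices may also be lost, and this need not track patient prognosis. All of this stands. It limits what can be said about mechanism and direction, but the choice of analysis set remains as stated.

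The protocol also has safeguards. The adjustment for differential mortality bears on falls, quality of life and other non-fatal outcomes. It does not bring back randomised patients dropped from the mortality analysis, and if mortality is itself judged per protocol, its trigger may be biased. All serious adverse events go to the independent safety committee, and nothing limits that review to per-protocol patients. It is therefore too strong to infer that every safety conclusion is biased: only the comparative adverse event rate falls under the sentence at issue.

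**Conclusion.** The point holds as a flaw in a stated rule. Per protocol is the only analysis set given for outcomes that carry a stated effectiveness objective and the comparative harms, and no as-randomised analysis of them is mentioned even as support.

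Bias is possible and its size and direction are unknown. The figures of 0.83 and about 40%, or 0.92 and about 12%, rest wholly on assumed mortality, exclusion rates and relative risk in the excluded. A reader might infer that the plan will produce a spurious survival benefit. The documents do not support that, because exclusions that are balanced, or unrelated to prognosis, would do little harm. Nothing in the document ensures such exclusions, however. The intention-to-treat composite, which contains death and first non-elective admission, is unaffected. The concern is greatest for mortality, admissions and adverse events.

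**What to change.** Change the sentence in the Statistical analysis section, and its counterpart in the analysis plan, so that secondary outcomes are analysed as randomised. This should cover at least mortality, admissions, falls, fractures and adverse events. Use the same generalised mixed model as for the primary outcome, with practice as a random effect and study centre as a fixed effect. Keep per protocol as a supportive analysis only. Report measures of tool uptake that exist only in the intervention arm, such as drugs continued despite a recommendation to stop, descriptively.

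The cost is one sentence in each document. No new data are needed and the sample size stays at 3542.
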